**Fig. 2 Fig2:**
[figure not shown]
Non-inferiority chart. The lines A–D represent mean and confidence interval of the differences in NRS-changes in the two treatment groups a and b. Examples A and B show that the agent a is inferior to agent b, while examples C and D confirm that agent a is non-inferior to agent b. IMP, investigational medicinal product; NRS, numeric rating scale

$${H}_{1}\to {H}_{2}\to {H}_{3}$$

The statistical chain of testing and decisions will be:*Test *$${H}_{1}$$*:* If part of the 95% confidence interval is below non-inferiority margin, we stop testing without any conclusion on efficacy. If the 95% confidence interval is above the non-inferiority margin, then we claim non-inferiority of methoxyflurane vs fentanyl and proceed with testing $${H}_{2}$$.*Test *$${H}_{2}$$*:* If part of the 95% confidence interval is below the non-inferiority margin, we stop testing without any further conclusion on efficacy. If the 95% confidence interval is above the non-inferiority margin, then we claim non-inferiority of methoxyflurane vs morphine and proceed with testing $${H}_{3}$$.*Test *$${H}_{3}$$*:* If part of the 95% confidence interval is below the non-inferiority margin, we stop testing without any further conclusion on efficacy. If the 95% confidence interval is above the non-inferiority margin, then we claim non-inferiority of fentanyl vs morphine.

The nominal significance level is set to 5%, and the non-inferiority margin is set to 1.3. Non-inferiority is determined based on a 1-sided equivalence *t*-test on the per protocol population and confirmed, for sensitivity reasons, on the modified intention to treat population.

We plan to compare the incidence of serious and non-serious adverse events between the groups using a chi-squared test or a Fisher exact test if necessary (expected frequency less than 5). We will summarize patient satisfaction and medical personnel view on practicality.

Demographic and baseline information of the three study groups will be compared using *t*-tests (means), Mann–Whitney *U* (medians), and chi-square (proportions) tests. If there are any significant differences, linear regression will be performed to adjust for significantly different covariates. No interim analysis will be performed.

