## Study rationale

The rationale of the PreMeFen-study is to provide evidence for earlier, safe, non-invasive pain management in the pre-hospital setting.

We aim to investigate whether regimens of:Inhaled low-dose methoxyflurane is non-inferior to IN fentanyl orInhaled low-dose methoxyflurane is non-inferior to IV morphine orIN fentanyl is non-inferior to IV morphine

in managing a variety of moderate to severe acute pain conditions in adult patients from 18 years of age administered by the EMS.

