## Methods

### Study design

We applied the Norwegian Clinical Research Infrastructure Network (NorCRIN) templates [18] to design a randomized, controlled, open-label, three-arm, non-inferiority, phase three drug trial. The trial will be performed according to the principles of the Helsinki Declaration. The randomization is 1:1:1 to the three treatment groups, with 90 patients in each group, totaling 270 patients. Patients in all treatment groups follow a treatment regime rather than receiving a single drug dose. For ethical reasons, a placebo arm was excluded. The study protocol was drafted in accordance with the Standard Protocol Items: Recommendations for Interventional Trial guidelines (SPIRIT) [19].

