### Sample size

The sample size with $$\alpha$$ = 0.05 and $$\beta$$ = 0.10 (90% power) was estimated using a two-sided *t*-test [11, 21, 22]. Expected pain reduction after 10 min was set to 3.77 for methoxyflurane, 2.54 for fentanyl, and 2.70 for morphine treatment regimen based on similar studies [11, 19, 20]. A common conservative standard variation of 2.20 was used. Non-inferiority margin is set to $${\delta }_{I}$$ = 1.3 based on [22, 23]. Sample size required to detect this difference 10 min after administration of IMP was estimated to be *n* = 88 in each arm. That gives a total number of participants of 264, and the plan is to include 3 × 90 = 270 patients per protocol allowing for two dropouts in each group, in total six dropouts, of the per-protocol population without losing power for the calculations of the primary endpoint.

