## Discussion

The study rationale is to provide evidence for early, safe, and effective pain management in EMS with non-invasive and fast-acting analgesics.

We aim to compare regimens rather than a fixed dose of the medicaments. With regimen we mean a flexible dosing of the allocated analgesic by titrating to effect, but only administer the allocated IMP. There are several reasons for comparing regimens rather than a fixed dose. Firstly, the route of administration differs to a large extent, with the inhalation of methoxyflurane being continuous depending on the patient needs, versus bolus dosing of the others. In addition, pharmacokinetics with bioavailability, *C*_max_, and *T*_max_ are different for all three IMPs. Furthermore, clinical needs and pain characteristics are heterogenous with individual needs for titration and redosing that cannot be foreseen and hence should be tailored with redosing within the allocated regimen. Finally, comparison of regimens will address the clinical setting where the interesting objective is to find whether the regimens of non-invasive methods are non-inferior to the existing IV morphine procedure. This will make the results relevant for decision-makers when implementing new procedures in pre-hospital pain management.

Our choice of a non-inferiority trial design is based on the expectation that IN fentanyl and inhalation of low-dose methoxyflurane are as good as (non-inferior to) IV morphine and that the first two will contribute to an earlier and more practical administration of the analgesics in the pre-hospital setting. Furthermore, it is of great interest to establish whether the self-administrated inhalation of methoxyflurane is as good as IN fentanyl, because it would ease the pain management in many acute pre-hospital settings.

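### The only named test of adverse event incidence is a test of equality, which at 90 per arm says little about serious or uncommon harms; interval estimates would say more

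*Protocol article*

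**What the plan says.** The Study rationale section says that the trial is meant to "provide evidence for earlier, safe, non-invasive pain management in the pre-hospital setting". The Discussion repeats this: "The study rationale is to provide evidence for early, safe, and effective pain management in EMS with non-invasive and fast-acting analgesics".

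For pain, the Statistics section requires the 95% confidence interval of the treatment difference to lie on the right side of a margin before non-inferiority is claimed. For adverse events, the same section names one method: "We plan to compare the incidence of serious and non-serious adverse events between the groups using a chi-squared test or a Fisher exact test", with Fisher's test used when an expected count is below 5. It gives no effect measure, interval or expected event rate for that comparison. It also does not say whether the test is pairwise or across all three arms. The only significance level stated is the general one: "The nominal significance level is set to 5%, and the non-inferiority margin is set to 1.3".

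The Study design section fixes the size, "with 90 patients in each group, totaling 270 patients", and the Sample size section derives it from the pain score alone.

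Table 4 also lists changes in sedation, respiratory rate and systolic blood pressure at 10 and 30 minutes as secondary endpoints, and an exploratory look at adverse events against co-medication. The Data monitoring committee section provides for a safety review at half recruitment.

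**The concern.** A chi-squared or Fisher test asks whether equal incidence can be rejected. It does not ask how large an excess of harm the data still allow. The result that favours a new regimen is failure to reject, and a small trial produces that result easily.

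This matters most for serious events. They are probably uncommon here, because the Adverse event section collects events only from the first dose to the end of the intervention. If the report gives only a p-value beside a non-inferiority finding on pain, a policymaker cannot tell whether an excess of one percentage point or of ten remains compatible with the data. For pain, the plan already judges whether one regimen is as good as another by an interval against a bound. For adverse events it names no interval.

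**Working it through.** **The plan's own figure.** There is no power or precision figure for safety. The stated 88 per arm concerns pain only. The closest reproduction is a two-sided 5% comparison with 90% power, SD 2.20 and difference 3.77 − 2.70 = 1.07: n = 2 × (1.960 + 1.282)² × 2.20² / 1.07² ≈ 89. Its derivation does not affect what follows, because 90 per arm is planned either way.

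**Inputs.** From the article: 90 per arm, 1:1:1 allocation, 5% level, chi-squared with Fisher when an expected count is below 5. Assumed: the tests are two-sided, about 90 per arm enter the comparison, and reference event rates lie between 1% and 20%.

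**Power under the stated rule, one pair of arms.** Power = Σᵢ Σⱼ Bin(i; 90, p₁) × Bin(j; 90, p₂) × 1{p-value ≤ 0.05}. With equal arms the smallest expected count is (i + j)/2, so Fisher applies whenever the two arms together have fewer than 10 events. Enumeration gives:

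| Reference rate | Doubling | Power | Tripling | Power |
|---|---|---|---|---|
| 1% | 1% v 2% | 0.4% | 1% v 3% | 2.4% |
| 2% | 2% v 4% | 3.7% | 2% v 6% | 15.8% |
| 5% | 5% v 10% | 23% | 5% v 15% | 63% |
| 10% | 10% v 20% | 47% | 10% v 30% | 93% |
| 20% | 20% v 40% | 84% | 20% v 60% | about 100% |

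**Why the first two rows are so low.** With no events in one arm, five in the other give a two-sided Fisher p = 2 × (90·89·88·87·86)/(180·179·178·177·176) = 0.059. Six give 0.059 × 85/175 = 0.029. So at least six events against none are needed, while a 2% rate yields 90 × 0.02 = 1.8 events on average.

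**Where power reaches 50%.** By the normal approximation this happens when p₂ − p₁ = 1.96 × √(2p̄(1 − p̄)/90), with p̄ the mean of the two rates.
- Doubling from 10.7%: p̄ = 0.161, and 1.96 × √(2 × 0.161 × 0.839/90) = 0.107, which equals the difference.
- Tripling from 3.9%: p̄ = 0.079, and 1.96 × √(2 × 0.079 × 0.921/90) = 0.079, which equals the difference.
- For 80% power, the corresponding rates are about 18.6% and 7.3%.

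**If the test is run across three arms.** A simulated 2-df chi-squared test (200,000 runs, one arm raised, no switch to Fisher) gives 25%, 50% and 88% power for a doubling from 5%, 10% and 20%. It gives 68% and 96% for a tripling from 5% and 10%. The pattern is the same.

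**What an interval would add.**
- 5/90 v 0/90: Fisher p = 0.059. The Wilson limits are 2.4% to 12.4% for 5/90 and 0% to 4.1% for 0/90. Newcombe's lower limit is 5.56 − √((5.56 − 2.40)² + 4.09²) = 0.4 points, and the upper is 12.4 points. Part of the disagreement with the p-value arises because Fisher's test is conservative and the two methods are not inversions of each other. The useful information is the upper limit.
- 5/90 v 5/90: Newcombe −7.5 to +7.5 points.
- 0/90 in one arm: exact upper 97.5% limit 1 − 0.025^(1/90) = 4.0%.
- Equal true rates: expected half-width 1.96 × √(2p(1 − p)/90), which is 6.4 points at 5% and 8.8 points at 10%.

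**The case against.** The strongest reply has four parts.

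First, the weakness depends on event rates that the article does not give, and the planned test covers non-serious events too. A reader might infer that non-significance is to be expected even if a regimen doubles or triples any harm. The table shows otherwise: a tripling from 5% is detected 63% of the time, a tripling from 10% is detected 93% of the time, and a doubling from 20% is detected 84% of the time. This stands, and it limits the point to serious or uncommon events.

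Second, a reader might take the test to be the trial's only between-arm safety analysis. It is not. Sedation, respiratory rate and systolic pressure are stated secondary endpoints, and a continuous measure fares much better: a 0.5-SD difference has 92% power at 90 per arm. This stands too. The test is the only one named for adverse event incidence, which those measures do not replace.

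Third, a reader might infer that the plan will treat p > 0.05 as proof of equal safety, or that a safety margin is missing. The article says neither. Its hypotheses and stated conclusion concern pain only, and safety appears as rationale. A missing margin contradicts nothing.

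Fourth, intervals and table layouts usually belong in the analysis plan, which is not shown and may contain them, and this kind of test is ordinary practice in a trial sized for efficacy. That is fair, and silence is not exclusion. But the article does choose and name a method for this comparison, and that method is poorly matched to the safety part of the rationale.

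**Conclusion.** The point holds in a limited form. The one method named for adverse event incidence cannot bound an excess of harm. At reference rates of about 1% to 2% it would almost always be non-significant under a doubling (power 0.4% to 4%) and usually under a tripling (2% to 16%). A non-significant result for serious or uncommon events therefore says little towards the safety part of the rationale. For common events the test is informative, from about 11% for a doubling and about 4% for a tripling.

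The figures assume 90 per arm in the comparison, two-sided 5% tests, and event rates that are not in the article. This is a worthwhile and inexpensive improvement in method. It is not an error, and it does not bear on the primary analysis.

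**What to change.** In the Statistics section, make estimation the basis of the adverse event comparison:

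- For the three pairs already used for efficacy (methoxyflurane v fentanyl, methoxyflurane v morphine, fentanyl v morphine), report the proportion of patients with at least one adverse event and with at least one serious adverse event.
- Give each risk difference with a two-sided 95% confidence interval (Newcombe or Miettinen–Nurminen), and the exact upper limit where an arm has no events.
- Keep the chi-squared or Fisher p-values as descriptive only, and state that non-significance will not be used to conclude equal safety.

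The cost is a paragraph of wording and a few table columns, with no new data or patients. The one drawback is that the intervals will be openly wide. A larger trial is not a realistic alternative: by the normal approximation, 80% power for 2% v 4% would need about 1,141 patients per arm. If the analysis plan already specifies these intervals, a sentence in the protocol pointing to it would be enough.

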### Endpoints

Primary endpoint is the change in NRS pain score measured prior to administration of IMP to 10 min after IMP administration; see Table 4 for secondary and exploratory endpoints.

**Table 4 Tab4:** Study endpoints

Primary endpoint	• Changes in pain score from T_0_ to T_10_
Secondary endpoints	• Changes in pain score from T_0_ to T_5_, T_20_, T_30_ and end of mission T_ED_ • Need for additional analgesia not in the regimen of the allocated treatment group • Differences in time arrival to administration of IMP registration of AE and SAE during study period until end of intervention • Time from ambulance personnel arrival to first measure > 2 points reduction in NRS from baseline • Change in level of sedation from T_0_ to T_10_ and T_30_ • Change in RR T_0_ to T_10_ and T_30_ • Change in SBP T_0_ to T_10_ and T_30_ • Likert scale of HCP satisfaction at end of mission • Likert scale of patient satisfaction at end of mission • Registration of AE and SAE during study period until end of intervention
Exploratory endpoints	• Analyze primary and secondary efficacy endpoints stratified by diagnosis or diagnosis groups • Proportion of patient receiving rescue treatment related to procedures (reposition of fractures, relocation, etc.) • Attempts of vascular cannulation access • Change in NRS and time to a significant NRS reduction compared to level of competence • Ambulance personnel competence and patient satisfaction • Analyze primary and secondary efficacy endpoints stratified by level of troponin after ED admission and sign of ACS on ECG at scene • Analyze AE and SAE in relation to concomitant therapy and other non-IMP determinants

*IMP* Investigational medicinal product, *AE* Adverse event, *SAE* Severe adverse event, *NRS* Numeric rating scale, *RR* Respiratory rate, *SBP* Systolic blood pressure, *HCP* Health care personnel, *ED* emergency department, *ACS* Acute coronary syndrome, *ECG* Electrocardiogram, *T*_*-x*_ Scene arrival, *T*_*0*_ Time of IMP administration, *T*_*5*_ 5 min after IMP administration, *T*_*10*_ 10 min after IMP administration, *T*_*20*_ 20 min after IMP administration, *T*_*30*_ 30 min after IMP administration, *T*_*ED*_ Time arrival emergency department or end of service

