### Statistics

The hypotheses in Eq. (1) will be tested and a conclusion of non-inferiority will be made if the 95% CI of estimated treatment difference fully lie above the inferiority margin; see Fig. 2. Hypotheses $${H}_{1}$$, $${H}_{2}$$, and $${H}_{3}$$ will be tested using the fixed-sequence procedure, to avoid inflating the significant level for the overall test. Accordingly, family-wise error rate will remain the same as the local nominal significance level *a*. The test will be performed in the following order:

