### Missing data

For non-inferiority calculation of the primary endpoint, missing data will be replaced using imputation. We will perform a linear regression adjustment for baseline pain.

Due to the pre-hospital circumstances with patients in pain and a situation of urgency, some missing data are to be accepted. The principal investigator is responsible for deciding whether participants with missing data are evaluable. Missing data are to be recorded and reported to maintain transparency.

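### Covariates are chosen by baseline significance tests, the deciding t-test leaves baseline NRS out of the model, and the standing of the baseline-pain regression is not stated

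*Protocol article*

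**What the plan says.** Three statements in the protocol article bear on the model for the primary endpoint.

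- **Deciding test (Methods, Statistics, text after Fig. 2).** "Non-inferiority is determined based on a 1-sided equivalence" t-test on the per-protocol population, with confirmation on the modified intention-to-treat population. No covariate is named.
- **Conditional adjustment (same section, last paragraph).** "Demographic and baseline information of the three study groups will be compared using" t-tests, Mann–Whitney and chi-square tests, and then: "If there are any significant differences, linear regression will be performed to adjust for significantly different covariates". The variables are not listed, and the outcome or conclusion that this regression serves is not given.
- **Baseline-pain adjustment (Methods, Missing data).** "For non-inferiority calculation of the primary endpoint, missing data will be replaced using imputation". The next sentence reads: "We will perform a linear regression adjustment for baseline pain". It carries no condition and no rank relative to the t-test.

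The decision rule in Statistics is that "a conclusion of non-inferiority will be made if the 95% CI of estimated treatment difference fully lie above the inferiority margin". It does not tie the interval to a particular estimator. The endpoint is a change score (Endpoints), so baseline NRS enters the outcome, but the t-test does not use it as a covariate.

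**The concern.** Under sound randomisation, a significant baseline difference is a chance finding, so testing for it answers no useful question. Adjustment pays when a covariate predicts the outcome, whether or not the arms differ on it. A rule driven by baseline p-values can bring in a variable unrelated to pain relief and leave out baseline NRS whenever it happens to be balanced. Taken alone, it would admit baseline NRS in only about 5% of pairwise comparisons.

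There is reason to expect baseline NRS to matter. Entry requires a score of at least 4 on a 0–10 scale, and the reduction cannot exceed the starting score.

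Two things are at stake. One is precision that the trial could have from data it already collects. The other is an adjusted estimate whose model is unknown until the baseline tests have been run and whose weight beside the t-test is not stated. Because H1, H2 and H3 are tested in a fixed sequence, a disagreement at an early step would also leave it unclear whether testing continues.

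**Working it through.** The article gives no figure on this point to reproduce. Its SD, arm size, margin and expected reductions serve as inputs.

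**Inputs from the article:** SD of change 2.20; 90 per arm; margin 1.3, read here as −1.3 for the difference in mean reduction; expected reductions 3.77 (methoxyflurane), 2.54 (fentanyl) and 2.70 (morphine); decision by 95% CI.

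**Assumptions, not in the article:** 5, 10 or 15 independent baseline variables; correlation of baseline NRS with change of 0.3–0.5; for the simulation, equal SDs at baseline and 10 min with correlation r = 0.3–0.7 between the two scores.

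**1. How often the rule changes the model.** The chance of at least one significant variable among k is 1 − (1 − p)^k.

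| k | one test per variable, p = 0.05 | three pairwise tests, p = 0.122 |
|---|---|---|
| 5 | 1 − 0.95^5 = 23% | 1 − 0.878^5 = 48% |
| 10 | 1 − 0.95^10 = 40% | 1 − 0.878^10 = 73% |
| 15 | 1 − 0.95^15 = 54% | 1 − 0.878^15 = 86% |

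The 12.2% comes from simulating three groups with pairwise z-tests. Direct simulation of all variables (20,000 replicates) gave 0.477, 0.726 and 0.863. The article does not say whether the tests are pairwise, so both columns are shown.

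**2. Precision forgone.** The SE ratio, ANCOVA to unadjusted change, is √(1 − ρ²), with ρ the correlation of baseline with change.

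- ρ = 0.3: √0.91 = 0.954, an SE about 5% smaller, worth 1/0.91 = 1.10, or 10% more patients.
- ρ = 0.5: √0.75 = 0.866, an SE about 13% smaller, worth 1/0.75 = 1.33, or 33% more patients.

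The unadjusted SE is 2.20 × √(2/90) = 0.328. The 95% half-width is 1.96 × 0.328 = 0.64, falling to 0.61 (ρ = 0.3) or 0.56 (ρ = 0.5).

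**3. Effect on the decision.** Two arms of 90 were simulated 20,000 times, taking non-inferiority as a 95% CI wholly above −1.3. Test-then-adjust used baseline NRS as the only candidate covariate. With equal SDs, ρ = √((1 − r)/2), so r = 0.3–0.7 corresponds to ρ = 0.59–0.39. This overlaps the range in step 2 but is not identical to it.

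| True difference | t-test passes | ANCOVA passes | test-then-adjust passes | t-test and ANCOVA disagree |
|---|---|---|---|---|
| −1.3 (at the margin) | 0.023–0.025 | 0.024–0.025 | 0.020–0.023 | 2–3% |
| −0.16 (2.54 − 2.70) | 0.93–0.94 | 0.96–0.99 | 0.94–0.95 | 4–6% |
| 0 | 0.98 | 0.99–1.00 | 0.98 | about 2% |

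The first row is the one-sided error, and test-then-adjust is slightly conservative there. Error rises to 0.034–0.039 only if the more favourable of the t-test and ANCOVA is picked afterwards.

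**4. Where in the sequence it matters.** On the article's expectations, H1 lies (1.3 + 1.23)/0.328 = 7.7 SEs from the margin and H2 (1.3 + 1.07)/0.328 = 7.2, so the model could hardly change either verdict. H3 lies (1.3 − 0.16)/0.328 = 3.5 SEs away. For H1 and H2 the choice matters only if methoxyflurane does worse than expected.

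**The case against.** The strongest reply is that the article names one deciding analysis. Only the t-test is said to determine non-inferiority. The conditional regression stands in the paragraph on baseline comparisons, and the baseline-pain regression stands under Missing data, where it may be part of handling incomplete data or a supportive analysis. A reader might infer that the t-test and the regression are both primary. The text does not support that: neither regression is called primary, and ranking supportive analyses is commonly left to the statistical analysis plan, which is not shown. This part of the objection stands. It leaves a regression that is promised but not placed, and the faulty covariate rule, which is stated outright.

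A reader might also infer inflated type I error. The simulation does not show it. The rule acts on baseline data, not outcomes, and nothing in the article permits choosing the favourable result afterwards.

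Three further limits stand. The loss of precision applies because the t-test decides; if the baseline-pain regression were the deciding analysis, that loss would vanish. The bound on reduction suggests a link between baseline NRS and change but not its strength, and the article gives no correlation. Finally, a high trigger rate is not itself a harm: power for a true difference of −0.16 is already about 0.93 with the t-test.

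**Conclusion.** The point holds in a limited form. Selecting covariates by baseline significance is unsound as published and makes the adjusted model data-dependent, with a trigger chance of 23–54% or 48–86% over 5–15 assumed independent variables, depending on how the tests are counted. The deciding t-test gives up a 5–13% smaller standard error if the correlation of baseline NRS with change is 0.3–0.5, which is an assumption. How the baseline-pain regression relates to the t-test is unstated, and the two would disagree in roughly 2–6% of trials under the simulated conditions. The harm is lost precision and an adjusted estimate of unclear standing. It is neither two competing primary analyses nor a false-positive rate above the nominal level. This is a cheap improvement, not a flaw that invalidates the design.

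**What to change.** By documented amendment, before database lock and before treatment codes are revealed to the statistician:

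- Make one prespecified ANCOVA the analysis for H1–H3: NRS change at T10 on arm and baseline NRS. Its 95% CI for each adjusted difference in reduction is read against −1.3.
- Delete the baseline significance tests and the adjustment that depends on them; describe baseline characteristics by arm instead.
- Keep the unadjusted t-test as a labelled sensitivity analysis.
- Replace the regression sentence under Missing data with a reference to this model.

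Baseline NRS is already in the schedule of activities, so no new data are needed. The cost is a small amendment to the stated primary test. Its timing needs care: the trial is open-label, and Trial status estimated that recruitment would be complete in April 2023, before the article appeared in September 2023. The Blinding section says the datasets are blinded for the statistician, which makes a credible amendment possible while that still holds.
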